## Abstract

**Introduction:**

High-speed boat operations expose personnel to slamming-induced impacts, which can lead to musculoskeletal injuries and cognitive impairments. Despite existing safety measures, regulations and protocols, the risk of injuries remains significant. The MultiAgency, prospective, exploratory, non-intervention, cohort Study on Human Impact Exposure oNboard high-speed boats study aims to investigate the nature and magnitude of these impacts, their acute and long-term health effects, and potential injury prevention strategies to improve operational safety and performance.

**Methods and analysis:**

This is an ongoing multicentre, prospective, non-intervention, observational cohort study. The first participant was enrolled on 23 August 2024. High-speed boat operators log self-reported pain data via a smartphone app, using a Visual Analogue Scale and pain drawings. Triaxial accelerometers are installed on boat hulls and worn by participants to measure impact exposure. Data analysis assesses correlations between exposure and reported pain, enabling the identification of risk factors and the development of safety guidelines for high-speed boat operations.

**Ethics and dissemination:**

The study has received ethical approval from the relevant ethics committees, including the Swedish Ethics Review Authority (no. 2022-04931-01). All participants will provide informed consent before enrolment. The findings will be disseminated through technical reports, articles in peer-reviewed journals, conference presentations and direct engagement with military and maritime stakeholders to enhance training protocols and safety measures.

**Trial registration number:**

NCT05299736.

STRENGTHS AND LIMITATIONS OF THIS STUDYThis study is a multicentre, prospective cohort design, allowing for a comprehensive evaluation of human impact exposure across diverse operational environments.The use of objective impact measurement through triaxial accelerometers enhances the accuracy and reliability of exposure data.The inclusion of self-reported pain assessments provides valuable subjective data on the effects of impact exposure, although it may be susceptible to recall bias.The study population is limited to professional high-speed boat operators, which may restrict the generalisability of findings to recreational users or other occupational groups.The observational nature of the study means that causality cannot be definitively established between exposure and health outcomes, necessitating further interventional research for validation.

## Introduction

 High-speed boat operations expose humans to slamming-induced impacts, where the boat hull hits the waves, transmitting significant impact forces through the boat to its occupants. The intensity and frequency of slamming impacts depend on a variety of factors, including the speed of the boat, the sea state and the design of the boat.^1^ Musculoskeletal injuries sustained during high-speed boat operations are typically caused by repeated exposure to whole-body impacts.^1 2^ The induced forces can bend, twist and compress the spine, causing vertebral fractures, disc herniations and distortion injuries. Slamming can also cause significant impact forces transmitted through the upper extremities, leading to injuries such as rotator cuff tears and wrist fractures.^3^ Moreover, these forces may affect the brain, leading to neurological symptoms and injuries, including cognitive effects and mild traumatic brain injury.^4^

Several studies have evaluated the effects of impact exposure on operator performance during high-speed boat transits.^5^ Post-transit, operators were found to have decreased running performance,^6^ increased inflammation as reflected by salivary cortisol^7^ and increased muscle damage as reflected by elevated levels of creatine kinase.^8^ Impaired cognitive functionality affecting operational readiness, even unconsciousness, has been reported.^1^ A recently published systematic review identified five scientific reports describing 3312 injuries sustained during 3467 person-years onboard high-speed boats.

Repetitive exposure to slamming may lead to chronic musculoskeletal disorders, pain conditions and disabilities. Long-term exposure to whole-body vibration is known to have detrimental cumulative effects on the intervertebral discs and increases the incidence of low-back pain.^9 10^ Additionally, slamming impacts can cause musculoskeletal injuries, particularly to the spine and lower extremities.^13 5 11^,^14^ To address the occurrence of these injuries, legal exposure regulations are in place, and operational restrictions have been implemented.^15^ However, littoral and amphibious operations often require rapid transits to transport operators, irrespective of weather conditions and sea states.

There are several reasons why human impact exposure onboard high-speed boats needs to be studied.

*Injury prevention*: researchers can identify effective strategies to prevent or mitigate injuries by examining the nature and severity of slamming impacts and their correlation to reported pain and risk of musculoskeletal injuries due to repeated exposure.^116^,^18^*Health and safety regulations*: understanding the nature and magnitude of impact exposure that may cause injuries can guide the development of relevant health and safety regulations for high-speed boat operations and help avoid unwarranted operational restrictions.^19^*Boat design and technology*: by studying impact exposure, researchers can identify areas for improved boat design and technology.^20^ For example, by developing better shock-absorbing materials or hull shapes, naval architects can help reduce the exposure to impact on the human body.*Training*: exposure to high, potentially harmful magnitudes of whole-body impacts has not been shown to have positive training effects. Knowing what magnitudes of exposure are sustainable can improve training routines and objectives.*Operational optimisation*: the slamming-induced impacts can also affect the performance of high-speed boats.^21^ By studying the nature and severity of slamming impacts, researchers can identify ways to optimise boat performance, such as adjusting speed or altering course in response to changing sea conditions. With a better understanding, operators can make better decisions, improving operational efficiency.

This prospective, multicentre, observational, cohort study on human impact exposure onboard high-speed boats aims to determine (1) the nature and the magnitudes of slamming-induced impacts on humans onboard and (2) the types and magnitudes of impacts that are potentially harmful.

## Methods and analysis

### Study design, setting and participants

This prospective, self-controlled, non-intervention, multicentre cohort study investigates the acute effects of slamming-induced impact exposure on high-speed boat operators’ musculoskeletal systems and cognitive functions. The study protocol is reported according to Strengthening the Reporting of Observational Studies in Epidemiology guidelines and was registered prospectively on ClinicalTrials.gov with the identifier NCT05299736.^22^ This study has been designed by the North Atlantic Treaty Organization (NATO) Science & Technology Organization, Research Task Group HFM-344. The recruitment of academic centres started in 2022 and the first participant was enrolled on 23 August 2024. We expect to close the inclusion of study participants before 30 June 2027. The schedule of participant enrolment, exposures and assessments is presented in table 1.

**Table 1 T1:** Schedule of enrolment, exposures and assessments

Timepoint	Study period							
	Enrolment	Allocation	Post allocation					Close-out
	*−t_1_*	0	*t_1_*	*t_2_*	*t_3_*	*t_4_*	*etc*	*t_90_*
Enrolment:								
Eligibility screen	X							
Informed consent	X							
Allocation		X						
Exposure:								
Slamming forces								
Whole body impacts								
Assessments:								
Questionnaire		X						X
Level of pain (VAS)		X	X	X	X	X	X	X
Pain character (pain drawing)		X	X	X	X	X	X	X

Timepoints *t* define days 1–90.

VAS, Visual Analogue Scale.

Eligible participants are military and civilian agencies, organisations and institutions that operate boats capable of hydroplaning speeds, have professional high-speed boat operators and allow the installation of accelerometer devices and data recording. The study will include operators in each centre between age 18 and 65 years who either operate or are being regularly transported onboard high-speed boats and have signed the informed consent form.

### Outcomes, data sources and measurements

#### Pain

Pain is a common symptom experienced by high-speed boat operators exposed to repeated slamming impacts, and it is a common reason that operators seek medical attention or modify their work activities.^1^ By studying the occurrence and duration of pain and its correlation in time after slamming-induced impacts, the study aims to assess the risks of injurious exposure. Pain can be monitored non-invasively using validated methods, such as the Visual Analogue Scale (VAS) or Numeric Rating Scale, which rate pain intensity, and pain drawings to assess pain location, duration and interference with activities.

In this study, self-reported pain will be logged daily through a smartphone application, PainDrawing (figure 1),^23^ adapted specifically for this project.^24^ The application is based on the Nordic Minister Council’s pain drawing form and a VAS. PainDrawing can be downloaded freely from Google Play and Apple AppStore and works offline and in flight mode. Reported pain data will comprise the following characteristics: location, pain modality, intensity and duration. Participants will be urged to log pain daily for the whole test period, regardless of whether they have been on board a boat or not. Participants will serve as their own controls by comparing periods of exposure onboard with periods of not working onboard.

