### Statistical methods

We will report descriptive statistics and calculate the mean, SD and range for human impact exposure and pain scores. Peak acceleration values, m/s^2^, will be registered in all three axes, x, y and z. A data analysis engine will categorise impacts with various combinations of the impact characteristics and allow for calculating correlations to registered pain experiences and various variables of the reported pain. We will use Pearson correlation coefficients to examine the association between human impact exposure and pain scores. We will also use linear regression to examine these associations while controlling for potential confounding variables (eg, age, sex, body mass index). Multivariate analysis based on analysis of variance (ANOVA) and logit models will be used to identify which characteristics of the impacts correlate to reported pain of various intensities, locations and durations after exposure. The results of the statistical analysis are expected to indicate which impact characteristics show a correlation to reported experiences of pain. Based on these findings, we will establish which impact exposure levels and characteristics are safe regarding physical and cognitive capabilities.

This analysis can also validate alternative ways of quantifying human exposure to discrete whole-body impacts and their potential relevance for predicting the risk of injury. Candidates for alternative units include calculated kinetic energy transferred or absorbed, J/kg, and the speed of this transfer, mechanical power, J/(kg·s). The analysis may need to include the calculated total change of speed and the distance during which the retardation of the boats and the human bodies occurs in each impact.

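### The daily pain score has no stated position relative to the day's transit, and on-board status is recorded only loosely, so the acute within-person contrast may be attenuated

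*Protocol article*

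**What the plan says.** The Pain section of the protocol article states that "self-reported pain will be logged daily through a smartphone application". The instruction on timing is "Participants will be urged to log pain daily for the whole test period", on boat days and other days alike. The footnote to Table 1 says that the timepoints "define days 1–90", with one VAS and one pain drawing at each. The pain fields listed are location, modality, intensity and duration.

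The aim is framed in time order. The Pain section refers to pain and "its correlation in time after slamming-induced impacts", and the Statistical methods section seeks the impact characteristics that "correlate to reported pain of various intensities, locations and durations after exposure". The comparison is within person: "Participants will serve as their own controls by comparing periods of exposure onboard with periods of not working onboard".

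Exposure is recorded at 600 Hz by one hull sensor and two kidney belts per boat, normally worn by the coxswain and the navigator (Exposure to impacts). Participants also include people who are regularly transported, and the Subgroup analysis section compares operators with passengers. The section on bias, confounding and compliance adds that the app asks, in free text, about relevant events on board and activities outside work. It sets compliance at 24 logged days or more per month.

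**The concern.** Exposure is timed to fractions of a second, but the outcome is placed only to the day. An operator who logs in the morning and then goes to sea gives a pre-exposure score for that day; one who logs in the evening gives a post-exposure score. Both follow the schedule, and both meet the compliance criterion, which counts days. For the morning logger, the first score after the transit arrives close to a day later, when short-lived pain may have faded or a new transit may be about to start.

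A related gap concerns the control periods. To know that a participant was not working on board on a given day, someone must record it. The belts identify two people per boat. For everyone else, and for transits on boats without a logger, the article describes only a free-text prompt about relevant events. An uneventful transit could go unmentioned and be counted as a day ashore.

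Both gaps would act on the same quantity, the exposed-minus-unexposed difference within a person. Both concern data collection, so later analysis can repair them only in part.

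**Working it through.** **The plan's own figure.** Inputs from Target sample size: difference 14 mm, SD 20 mm, 80% power, alpha 0.05 (taken as two-sided), one operator in six with an acute episode. Two-sample formula: 2 × (20 × (1.960 + 0.842) / 14)² = 32.04 per group; 32.04 × 6 = 192.2. The stated 192 is reproduced. No input concerns when the daily score is taken.

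**Dilution under calendar-day pairing.** Let f be the share of boat-day scores entered before the transit. The documents do not give f. Assume a rise of 14 mm after a transit, pre-transit scores that carry none of it, and no carry-over. The observed same-day contrast is 14 × (1 − f):

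| f | contrast |
|---|---|
| 0 | 14.0 mm |
| 0.25 | 14 × 0.75 = 10.5 mm |
| 0.50 | 14 × 0.50 = 7.0 mm |
| 0.75 | 14 × 0.25 = 3.5 mm |

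**Can the sign change?** Take alternating boat and shore days. Let c be the share of the rise that remains from an evening to the next morning, and again from that morning to the evening. In the steady state, the scores in units of 14 / (1 − c⁴) are:

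- boat day: morning c³, evening 1;
- shore day: morning c, evening c².

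The difference is 14 / (1 − c⁴) × [f(c³ − c) + (1 − f)(1 − c²)], which simplifies to 14 / (1 + c²) × [(1 − f) − f·c].

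- c = 0: this is 14 × (1 − f), which is never negative.
- c = 0.5: 11.2 × [(1 − f) − 0.5f], giving +7.0 mm at f = 0.25, +2.8 mm at f = 0.50 and −1.4 mm at f = 0.75.
- The sign changes only when f exceeds 1 / (1 + c): 0.80 for c = 0.25, 0.67 for c = 0.5, 0.57 for c = 0.75.

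A cruder version sets the pre-transit score on boat days to zero residual. It gives −2.6 mm at c = 0.5, f = 0.75 and −2.2 mm at c = 0.75, f = 0.50. It overstates reversal when carry-over is strong, because it ignores pain left from the previous transit. In the full version, reversal always needs more than half of the entries to be pre-transit.

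**Misplaced on-board days.** Assume that 30% of on-board days have no logger data and are counted as unexposed, over 90 days.

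- 20 on-board days: 20 × 0.3 = 6 misplaced; 6 / (70 + 6) = 7.9% of control days.
- 45 on-board days: 45 × 0.3 = 13.5 misplaced; 13.5 / (45 + 13.5) = 23.1% of control days.

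If misplaced days carry the same 14 mm rise and every score is post-transit, the contrast falls to 14 × (1 − 0.079) = 12.9 mm and 14 × (1 − 0.231) = 10.8 mm. The 30%, the 20 and the 45 are all assumptions.

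**The case against.** The strongest reply is that the article sets no rule that pairs scores by calendar date. A reader might infer from the day-level timepoints that a pre-transit score is treated as that day's response. The text does not say so: it speaks of pain after exposure and compares periods rather than dates. In a long block on board with some carry-over, morning scores after the first day would already reflect earlier transits. The app may store entry times, and the full protocol, app instructions or SAP may set a reminder hour and a linking window. With stored times, the next morning's entry is a genuine post-transit score. Pain duration is also collected.

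Much of this stands. Dilution depends on how scores are paired, and the article does not show that entry times are missing. What remains is that a SAP can choose a lag but cannot create a score closer to the transit than the one entered. Time stamps fix the order, not the delay. The article does not say how duration is dated, so it cannot be counted on to close the gap.

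It might also be inferred that a transit without a logger is indistinguishable from a day ashore. That goes too far, because the free-text prompt may reveal it. But a prompt about relevant events is not a daily record of presence.

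**Conclusion.** The point holds as a weakness in data collection that should be corrected while enrolment is open. The stated aim needs scores taken after exposure and a reliable split between days on board and days ashore; the described procedure secures neither. If pairing is by calendar day, the expected result is attenuation: from 14 mm to 10.5 mm with a quarter of boat-day scores pre-transit, and to 7 mm with half. Linking by entry time avoids the wrong order but leaves a lag of up to about a day for morning loggers. Misplaced on-board days would attenuate the contrast further, on assumed shares.

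Every size given here is illustrative. The 14 mm is the plan's minimally important difference for back pain, not an expected rise after a transit, and the documents give neither the share of pre-transit entries nor the share of unlogged days.

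Two stronger conclusions are not supported. A reader might infer that the effect could be reversed. In the illustration that needs carry-over into the next day together with a majority of pre-transit entries, and neither is established. A reader might also infer that 192 participants are too few. That figure reproduces from its stated inputs and does not depend on log timing.

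**What to change.** - **Timing.** Ask for the daily entry in the evening, and on boat days after the last transit, with the app reminder set to match. State this in the Pain section and in Table 1.
- **Linking.** Use the stored entry time, or store it if the app does not yet do so. Link each score to the impacts recorded since the previous entry, not to the calendar date.
- **On-board status.** Alongside the free text, add a structured daily item: on board a high-speed boat today (yes/no), which boat, belt worn (yes/no).
- **Missing exposure.** Class on-board days without logger data as exposure missing, not as unexposed.

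The cost is a reminder setting, a few tap items in an app already adapted for this project, and a few seconds more per participant per day. Participants enrolled since 23 August 2024 will lack the new items and should be distinguishable in the analysis. Inclusion is expected to run until about 30 June 2027, so later participants can still benefit.

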### Target sample size

A recent systematic review of five studies reported 1.1 injuries per person per year serving as high-speed boat operators.^5^ Our study follows operators for at least 2 months, estimating that one of six operators may experience one acute episode with musculoskeletal injury. The Minimally Clinically Important Difference for back pain VAS is 14 mm, and the SD is 20 mm.^27^ Consequently, a minimum number of 192 participants would be necessary to reach 80% power (1 minus type II error probability) at a 0.05 significance level (type I error probability) if followed for 2 months.

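### The self-control rule sorts time by where the operator is, not by time since exposure, so boat-caused pain felt ashore counts in the control periods and biases the within-person contrast toward no harm

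*Protocol article*

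**What the plan says.** The article's Study design section makes self-control part of the design: "This prospective, self-controlled, non-intervention, multicentre cohort study investigates the acute effects of slamming-induced impact exposure". The Pain section gives the only definition of what is compared: "Participants will serve as their own controls by comparing periods of exposure onboard with periods of not working onboard". No onset lag, post-exposure risk window, washout or rule for days ashore because of pain goes with it.

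Three other statements bear on this rule:

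- The Pain section states the aim as looking forward from the impact: "By studying the occurrence and duration of pain and its correlation in time after slamming-induced impacts".
- The same section says of pain that "it is a common reason that operators seek medical attention or modify their work activities".
- Statistical methods plans models to find "which characteristics of the impacts correlate to reported pain of various intensities, locations and durations after exposure".

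Pain is logged on all days: "Participants will be urged to log pain daily for the whole test period, regardless of whether they have been on board a boat or not". The section on risk of bias, confounding factors and compliance covers dissimulation, injuries from other activities, pre-existing pathology and poor logging. It mentions neither carry-over of pain nor absence caused by pain.

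**The concern.** A self-controlled comparison needs control time that is free of the effect under study. Here time is classified by the operator's location. Two routes that the article itself recognises then move boat-caused pain into the control time:

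1. **Carry-over or delay.** Pain that begins or persists after leaving the boat is recorded on days not working onboard.
2. **Exposure that depends on the outcome.** An operator who stays ashore because of boat-caused pain turns planned onboard days into painful control days.

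Both routes push the contrast the same way, toward no harm or apparent benefit from boat work. Adjusting for age, sex and body mass index cannot repair this, because the misclassification lies within the person. A larger sample only makes the biased contrast more precise. The study intends to say which exposures are safe, and for that purpose a bias toward no harm is the unsafe direction.

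**Working it through.** **Plan's own figures.** Target sample size cites a review that "reported 1.1 injuries per person per year serving as high-speed boat operators". Over 2 months this is 1.1 × 2/12 = 0.183 episodes per person. The chance of at least one is 1 − exp(−0.183) = 0.168, which agrees with the stated one in six. The sample size also reproduces: 2 × (20 × (1.960 + 0.842)/14)² = 32.04 per group, and 32 × 6 = 192. It does not depend on the point made here.

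**Inputs.** From the article: 1.1 episodes per person-year and 90 days of follow-up (Table 1). Assumed, because the article gives none of them: rota, onset lag, pain duration, and the chance of staying ashore on a painful day. All pain is taken to be caused onboard, so a valid contrast must show more pain with exposure.

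**Hand calculation, nobody ashore.** Let h be the episode rate per onboard day: h = (1.1/365) / (fraction of days onboard). For each onboard day of the rota on which an episode can start, count the painful days that fall onboard and off-boat. Then:

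- painful share of onboard days = h × (onboard pain-days summed over start days) / (onboard days per cycle)
- painful share of off-boat days = h × (off-boat pain-days summed over start days) / (off-boat days per cycle)

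*4 on/4 off, same-day onset, 7 days of pain.* h = 0.00301/0.5 = 0.00603. Starts on onboard days 1 to 4 give 4, 3, 3, 3 = 13 onboard pain-days and 3, 4, 4, 4 = 15 off-boat.
- Onboard: 0.00603 × 13/4 = 1.96%
- Off-boat: 0.00603 × 15/4 = 2.26%
- Sign reversed. A simulation of 20,000 persons over 90 days gives 1.88% against 2.14%. It is slightly lower because nobody starts in pain and episodes do not overlap.

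*14 on/14 off, same-day onset, 7 days of pain.* Eight start days keep all 7 pain-days onboard (56) and the last six keep 6 + 5 + 4 + 3 + 2 + 1 = 21. That is 77 onboard and 98 − 77 = 21 off-boat.
- Onboard: 0.00603 × 77/14 = 3.31%
- Off-boat: 0.00603 × 21/14 = 0.90%
- Diluted, not reversed. Simulated: 3.11% against 0.81%.

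*5 on/2 off, next-day onset, 3 days of pain.* h = 0.00301/(5/7) = 0.00422. Pain-days are 10 onboard and 5 off-boat.
- Onboard: 0.00422 × 10/5 = 0.84%
- Off-boat: 0.00422 × 5/2 = 1.05%
- Reversed by delay and carry-over alone. Simulated: 0.83% against 1.05%.

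*Pain on the exposure day only.* All pain falls onboard and the rule works.

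**Simulation with pain-driven absence.** On each painful day, half of the operators stay ashore.

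| Rota | Onset | Pain lasts | Onboard | Off-boat | Direction |
|---|---|---|---|---|---|
| 4/4 | same day | 7 days | 1.24% | 2.77% | reversed |
| 14/14 | same day | 7 days | 1.90% | 2.11% | reversed |
| 28/28 | same day | 7 days | 2.03% | 1.83% | correct, nearly erased |
| 14/14 | same day | 3 days | 1.09% | 0.63% | correct, diluted |
| 14/14 | next day | 7 days | 1.40% | 2.45% | reversed |
| 5/2 | next day | 7 days | 0.97% | 4.23% | reversed |

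With next-day onset and half ashore, every rota tried reversed.

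**The case against.** The best defence is that one design sentence is being read as an analysis rule. It speaks of periods without defining them, and a period could be taken to include the time after exposure. Statistical methods contains no onboard versus off-boat comparison of pain-days. It relates impact exposure and impact characteristics to pain, refers to "reported pain of various intensities, locations and durations after exposure", and derives safe levels from those models. An unseen analysis plan may define lags and windows, and an article need not. The sizes above also rest on invented rotas and absence rates: changing work activities is not the same as half of those in pain staying ashore.

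Much of this stands. A reader might infer that the study's exposure limits rest on the contaminated contrast. The article does not say so, and its exposure–pain models could use lagged exposure. A reader might also infer that the result will come out reversed. The documents do not support that, because sign and size depend on inputs they do not give.

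The defence does not remove the point. The complaint is not that a window is missing. The article positively defines control time as time not working onboard, this is its only definition of the self-control that the design is named for, and it conflicts with the article's own account of pain after exposure. Nothing in Statistical methods withdraws or qualifies it.

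**Conclusion.** The concern holds for the within-person contrast as the Pain section states it. The direction follows from the rule: delayed or lasting pain, and pain-driven absence, both move boat-caused pain into control time, so the contrast is biased toward no harm.

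The size is driven by assumptions. Across the settings tried, the effect ranges from intact (pain on the exposure day only), through diluted (long blocks, nobody ashore), to reversed (short rotas with 7-day pain, or next-day onset with half ashore).

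The correlation, regression, ANOVA and logit models share the bias only if they pair pain with same-day exposure, which the article leaves open. It is a correction to settle before analysis, not evidence that the study's conclusions are already unsound.

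**What to change.** **In the Pain section**, define exposed and control time by time since last impact exposure. A pre-stated window after exposure counts as exposed, wherever the operator then is.

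**In Statistical methods**, take new-onset pain as the outcome: the first painful day after a pain-free day, or a rise of at least 14 mm (the article's own minimal important difference) over the previous log. Relate it, on at-risk days, to the same person's impact exposure over a fixed preceding window. Add a sensitivity analysis of the window length.

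Do not add a sensitivity analysis that drops only the off-boat days after a pain onset. That removes painful days from one side, selects on the outcome and pushes the contrast toward harm. If post-onset days are excluded, exclude them onboard and off-boat alike.

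Add carry-over and pain-related absence to the listed sources of bias.

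**Cost.** Wording only, since daily pain logs and acceleration recordings are already planned and inclusion is expected to stay open until mid-2027. There will be somewhat fewer informative days, and the window must be chosen in advance. On short rotas a long window can use up the control time: with 5 on/2 off, a window of 2 days or more after exposure leaves none. The analysis would then rest on day-to-day variation in the amount of exposure.
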